### Impact Studies

Two impact studies will be conducted: the cost of the diagnostic odyssey will first be estimated. It will include the cost of all diagnostic procedures from the first genetics consultation, to inclusion in the DEFIDIAG project (period 1 of Figure 1). The impact of genomic analyses on follow-up will also be assessed. It will be based on a before-after study (period 3 compared to period 1) and will include treatment and diet as well as rehabilitation, psychological and medico-social follow-up.

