Specifically, the primary objective of this study is to compare the percentage of causal genetic diagnosis identified by GS performed on a trio (the patient and both parents) (GST), to the use of the current French reference minimal strategy (Fragile X + CMA + 44GPS) in ID patients attending a first genetics consultation. Secondary objectives focus on the diagnostic yield, and include the following:• To compare the percentage of ID causal diagnosis identified by GST, to GS in the proband only (i.e., genome in solo, GSS) in a subgroup of randomized patients attending for a first genetic investigation. This evaluation is useful because in genetic counseling, both parents are not always available.• To describe the estimated additional diagnostic yield that would be obtained at each step in sequential analysis of the GS data: for the minimal 44GPS gene panel, the list of genes known to be associated with disease from OMIM (referred to simply as OMIM), and ES, in patients attending for a first investigation (never-explored patients) and in patients who have already undergone investigations (previously-explored patients).• To compare the percentage of causal diagnosis of ID identified by GST to that obtained with the French reference minimal strategy in various subgroups (defined according to age, severity of ID, presence of major non-cerebral manifestations or epilepsy), for patients with ID attending for a first genetic investigation (never-explored patients).• To compare the percentage of causal structural changes (CNV, balanced structural variants) identified by GST versus CMA.• The DEFIDAG study also aims to compare the reference strategy, GST and GSs, in terms of costs and effectiveness for the causal diagnosis of ID in patients with ID of unknown etiology, attending for a first genetic investigation.• Finally, three impact studies are planned. The first will estimate the costs associated with searching for a molecular diagnosis that could potentially be avoided by performing GS as the first line approach. The second will evaluate the impact on the frequency and type of medical, medico-social and psychological care in the year following the release of GS results, compared to care during the year prior to inclusion, in particular in patients who were already engaged in a diagnostic process prior to being invited to participate in the DEFIDIAG study. The third impact study will be performed in two centers, and will use a qualitative approach, namely interviews with a sample of parents, to explore: 1) the burden experienced by the parents, 2) emotional adjustment of the patient and the parents to the results of genetic tests, and 3) the patient and parents’ perception of the future.

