**FIGURE 1 F1:**
[figure not shown]
Impact study procedures and schedule (DEFIDIAG study). The figure represents the key timepoints for patient visits in the inclusion centers (inclusion in the study, delivery of results, 12-months post-delivery visit), which also correspond to the time of the interviews between either a sociology or psychology researcher and the parents/patients who agreed to participate in the qualitative impact study. The figure also shows the three periods considered for cost estimation (period 1: before inclusion; period 2: waiting for results; period 3: during the 12 months following the results) and, for each of these periods, the different elements collected from the care teams and families in order to have the examinations carried out (for the three periods) and those envisaged with each of the strategies to confirm the diagnosis (period 2).

**TABLE 1 T1:** Correspondence between objectives and target population (DEFIDIAG study).

Eligible index cases (*n* = 1,275)	
**Index cases with undiagnosed ID coming for the first time for a genetic investigation (*n* = 637)**	**Index cases with undiagnosed ID already investigated (*n* = 637)**
Primary objective: Compare the percentage of genetic causal diagnosis identified in ID patients by performing trio GS analysis vs. the use of the current French reference minimal strategy	
Secondary objective: diagnostic yields	
•Compare the percentage of ID causal diagnosis identified by GST vs. the reference strategy in different subgroups (defined according to age, or clinical manifestations)	
•Compare the percentage of causal structural changes identified by GST vs. chromosomal microarray analysis	
•Compare the percentage of ID causal diagnosis identified by GST vs. GSS in a subgroup of randomized patients (*n* = 196)	
Secondary objective: Describe the estimated additional diagnostic yield that would be obtained at different steps of sequential analysis, for the 44 gene panels, OMIM and exome analysis	
Secondary objective: Assessing the efficiency of the three strategies (the reference minimal strategy; GSs; GS_T_)	
	Secondary objective: Estimate the cost of the diagnostic odyssey that could be potentially avoided by first-line genomic analysis

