#### Secondary Outcomes

• Efficacy in terms of diagnostic yield: identification of causal structural changes• Efficiency: estimation of the incremental cost-effectiveness ratio, expressed in terms of cost per additional positive diagnosis.• Quantitative impact studies• Cost of the diagnostic odyssey: mean cost related to the iterative search for a diagnosis in the previously investigated population.• Change in follow-up: criteria will be the change in the number and type of medical, medico-social, rehabilitative, and psychological care induced by the results of the trio genomic analyses.• Qualitative impact studies: A sociologist and a clinical psychologist will explore the consequences on the family, and on the personal, professional and social life of the parents who take care of a child or an adult with ID, as well as the emotional adjustment and possible information overload for the parents at the various stages of the study (inclusion, results rendering, 12 months after receiving results).

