The strategy based on GST is expected to yield a diagnosis in at least 60% of patients with ID versus 30% with the reference minimal strategy in the population of patients attending for a first genetic investigation (never-explored patients). However, the strategies will be compared in 7 subgroups: 1) 3 defined by age: children <2 years old/2–5 years/>5 years; 2) 4 subgroups of patients defined according the severity of ID, and/or 3) with associated manifestations:1) mild ID associated with another sign, 2) moderate to severe ID, 3) ID with major non-cerebral abnormality, and 4) ID associated with epilepsy The smallest sub-group (subjects with mild ID associated with another significant sign) should represent around 15% of the total population, and the difference between the GST and the reference strategy in this particular subgroup can be assumed to be less than 15%. In addition, it is assumed that fewer than 1% of diagnoses identified with the referral minimal strategy will not be identified by the GST. Finally, we will also compare GST and GSS in a subgroup of randomized patients referred for the first time. For this specific comparison, a difference of 7% is expected, and <0.1% of diagnoses identified by GSS and not by GST. Considering these 9 planned comparisons (8 comparisons between GST and the reference strategy and 1 between GST and GS), the one-sided alpha risk is fixed at 0.00278. Based on these hypotheses, and a power of 80%, among patients seen for a first genetic investigation (50% of the population to be recruited), 41 patients are required for the main comparison, and 91 patients with mild ID + other syndrome are necessary. To recruit this number of patients, we estimate that it will be necessary to screen 607 patients attending for a first referral. A subgroup of 196 patients will be randomized to undergo GSS in addition to GST plus the reference minimal strategy. The sample size for this subgroup will be sufficient to compare GST and GSS in terms of diagnostic yield, as well as in terms of efficiency (a sample size over 150 is usually deemed sufficient). As we intend to include 50% of patients attending for a first genetics evaluation (never-explored patients), and 50% of patients who have already been investigated (previously-explored patients), a total of 1,214 patients are necessary. Considering that approximately 5% of samples will not be analyzable, it will therefore be necessary to include 1,275 index cases plus both their parents, for a total of 3,825 participants.

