#### Impact Studies

The costs of finding a diagnosis will be described only in the population of patients who had previously had genetic investigations (50% of the 1,275 index cases), as the mean and standard deviation, if normally distributed, or as median and interquartile range otherwise.

The analysis of the impact of genomic analysis on medical, medico-social, rehabilitation and psychological follow-up after the results are made known, will be performed separately in the previously-explored population (50% of the 1,275 index cases) on the one hand, and in the population attending for a first genetics investigation on the other hand (never-explored patients). Frequencies of follow-up changes between the period prior to inclusion and the period following the results will be calculated with associated 95% confidence intervals. A global analysis will then be performed, regardless of the results of GST. Sub-analyses will be conducted according to the result of GST: positive, negative or uncertain.

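### The diagnostic-odyssey cost is measured gross in all previously explored patients, although the objective is the cost that first-line GS could avoid

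*Protocol article*

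**What the plan says.** The Introduction gives the aim of the first impact study as estimating the "costs associated with searching for a molecular diagnosis that could potentially be avoided by performing GS as the first line approach". Table 1 repeats it, in the column for previously explored patients: "Estimate the cost of the diagnostic odyssey that could be potentially avoided by first-line genomic analysis".

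The measure is then fixed in four places:

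- **Endpoint** (Secondary Outcomes): "mean cost related to the iterative search for a diagnosis in the previously investigated population".
- **Content** (Methods, Impact Studies): "It will include the cost of all diagnostic procedures from the first genetics consultation, to inclusion in the DEFIDIAG project". This is period 1 of Figure 1.
- **Population** (Data Analyses, Impact Studies): "The costs of finding a diagnosis will be described only in the population of patients who had previously had genetic investigations". That is half of the 1,275 index cases, summarised as mean and SD or median and IQR.
- **Who these patients are** (Table 1): "Index cases with undiagnosed ID already investigated".

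The same Data Analyses section also says: "Sub-analyses will be conducted according to the result of GST: positive, negative or uncertain". That sentence closes the paragraph on changes in follow-up. The cost paragraph before it has no such split.

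**The concern.** An avoidable cost needs a counterfactual: what would not have been spent had GS been done first. The plan has no step that turns past spending into avoided spending. Two features push the figure upward.

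1. Where GST is also negative at inclusion, it gives no reason to think that GS at the start would have supplied the diagnosis. At most, the genetic tests that GS replaces would have been saved. The rest of the search cannot simply be counted as avoided.
2. The group contains only patients whom earlier testing left undiagnosed. Those whom standard testing diagnosed are absent, so the mean describes searches that had failed up to inclusion.

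The Ethics and Dissemination section expects the cost-effectiveness and impact studies to show cost savings, and offers them in support of a decision on first-line GS. A gross cost read as an avoidable cost would tilt that argument in favour of GS.

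**Working it through.** The documents state no odyssey cost, no avoidable share and no GST yield in previously explored patients. There is thus no stated figure to reproduce, and the size has to be derived under assumptions.

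**Inputs from the Population section** (never-explored patients): GST is "expected to yield a diagnosis in at least 60% of patients with ID versus 30% with the reference minimal strategy". Fewer than 1% of reference diagnoses are assumed to be missed by GST.

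**Step 1: GST-positive share among reference-negative patients, q.**

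q = (GST yield − reference yield + share found only by the reference) / (1 − reference yield)

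- Nothing missed: (60 − 30)/70 = 42.9%.
- 1% of reference diagnoses missed, which is 0.3% of patients: 30.3/70 = 43.3%.
- The 1% read as a share of all patients: 31/70 = 44.3%.

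So q is 43–44% on any reading. This carries never-explored yields over to previously explored patients, which is an assumption.

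**Step 2: ratio of gross to avoidable cost.** Let k be the mean cost in GST-negative patients divided by that in GST-positive patients. Let s be the share of GST-negative cost that is still avoided because GS replaces tests.

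Ratio = [q + (1 − q)k] / [q + (1 − q)k·s]

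With k = 1 and s = 0 this is 1/q: 1/0.429 = 2.33, 1/0.433 = 2.31, 1/0.443 = 2.26.

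**Step 3: vary the assumptions, with q = 0.443.**

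| k | s | Ratio |
|---|---|---|
| 1 | 0 | 2.26 |
| 1 | 0.25 | 1.72 |
| 1 | 0.5 | 1.39 |
| 1 | 0.75 | 1.16 |
| 1 | 1 | 1.00 |
| 0.5 | 0 | 1.63 |
| 2 | 0 | 3.52 |

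**Step 4: vary the yield of earlier testing** (k = 1, s = 0, GST 60%). The Introduction puts Fragile X plus microarray below 20% and exome at up to 40%.

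- Earlier yield 20%: q = 0.50–0.51, ratio 1.95–2.0.
- Earlier yield 40%: q = 0.33–0.35, ratio 2.86–3.0.

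The 60% is stated as a minimum. At 65% against a 30% earlier yield, q is 0.50–0.51 and the ratio 1.94–2.0.

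**The case against.** The other side has five fair arguments.

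- **The wording is cautious.** The objective says potentially avoided, and the analysis only describes costs. A reader might infer that the plan will report the whole sum as saved, but no sentence says so, and the total can be read as an upper bound. This stands, although nothing labels it as one.
- **A negative GS still saves money.** The Introduction presents GS as replacing microarray, panel and exome tests and as a single molecular investigation. Some saving after a negative GS is thus part of the plan's premise. This stands, and it rules out an unconditional multiplier.
- **The first-line comparison is made elsewhere.** The cost-effectiveness study uses randomised first-referral patients, and GS itself is micro-costed. A reader might infer that the mean from this cohort will be applied to every first-line patient, with a larger overstatement. The plan makes no such extrapolation: it confines the cost to previously explored patients.
- **Period 1 stops at inclusion.** Later search costs that early GS might have spared are left out. This works in the opposite direction, by an unknown amount.
- **A condensed article leaves detail to the full plan.** That would answer a missing detail. Here endpoint, content, population and summary are all stated, and together they give a quantity other than the one in the objective.

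One caution also applies to the remedy. A positive GST at inclusion does not prove that GS at the first consultation, possibly years earlier, would have been positive.

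**Conclusion.** The mismatch holds. The objective is avoidable cost. The stated measure is gross past cost in all previously explored, undiagnosed patients, with no link to the GST result, and it is likely to overstate what first-line GS could avoid.

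The size is conditional. It is about 2.3-fold if only GST-positive patients' costs are avoidable, costs are equal by GST result, and never-explored yields carry over. It is about 1.4-fold if half of the GST-negative cost is avoided as well, and there is no overstatement if all of it is. Across the cost ratios tried at a 44% GST-positive share, the range is about 1.0 to 3.5. A flat claim of two- to threefold is not supported, because the documents give neither the avoidable share nor cost by GST result.

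This concerns a secondary, descriptive analysis and leaves the diagnostic comparison untouched. It should be corrected because the figure is meant to inform a policy decision.

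**What to change.** 1. Report period 1 cost by GST result (positive, negative, uncertain), using the split already planned for follow-up changes.
2. Define avoidable cost as the period 1 search cost in GST-positive patients plus, in GST-negative patients, only the genetic tests that GS would replace.
3. Label the all-patient total an upper bound. State that it describes previously explored, undiagnosed patients and is not a per-patient saving for a first-line population.
4. State as limitations that costs after inclusion are not counted, and that a GST result at inclusion stands in for one at the first consultation.

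No new data are needed: earlier examinations are entered in the e-CRF at inclusion, and GST is planned for every index case. The price is slightly more analysis, a rule for which tests GS replaces, and a less favourable headline cost.

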Secondary objective: Estimate the frequency and nature of changes in medical follow-up of the patients, but also in medico-social, rehabilitation, and psychological follow-up in the first year after the reporting of GS analyses compared to the period before the inclusion	
Secondary objective: Evaluate the burden experienced by the parents, 2) the parents’ emotional adjustment to the primary genetic tests results, and 3) the parents’ perception of the future	

GS_T_: genome sequencing—trio analysis; GS_S_: genome sequencing—proband only.

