#### GS Results Visit and Subsequent 12 months Follow-Up

When the results become available, and regardless of the results (positive or negative), the clinical geneticist who included the patient (and parents) will inform patient/family about the results of the GS during a dedicated visit. These results will be made available approximately 9 months after inclusion in the study. If the study identifies one or several class 3+, 4, or 5 variation(s), the clinical geneticist will explain the type of associated medical condition, its mode of inheritance and the risk of recurrence for a future pregnancy, as well as the modalities of care. All information (examinations, medical or non-medical treatment, medico-social follow-up, etc.) will be collected by the geneticist, assisted by a CRT. The diary kept by the families will be retrieved and integrated into the e-CRF. A new diary will be given to the family for the subsequent 12 months, and the phone contact by the CRT is planned. If the parents or adult with mild ID agreed to participate in the qualitative study, the sociologist/psychologist will then contact them to check that they all still agree to continue the interviews and organize the second interview.

Twelve months after the GS results are made known to the patient, a final visit at the hospital will be organized (this visit can be replaced by a telephone contact, if necessary) to assess the medical condition, collect any results and retrieve the diary. If the parents agreed to participate in the qualitative study, once again, the sociologist/psychologist will then contact them to check that they all still agree to continue the interviews and organize the third interview.

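### The before-after study of care has two incompatible baselines: the year before inclusion in the objective, and the span from first genetics consultation to inclusion in the methods

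*Protocol article*

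**What the plan says.** - **Objective (Introduction, second impact study).** Care is assessed "in the year following the release of GS results", "compared to care during the year prior to inclusion". Both windows are one year.
- **Methods (Impact Studies, after Medico-Economic Evaluation).** The odyssey-cost study covers procedures "from the first genetics consultation, to inclusion in the DEFIDIAG project (period 1 of Figure 1". The same paragraph then says of the follow-up study: "It will be based on a before-after study (period 3 compared to period 1".
- **Figure 1 caption.** The periods are "period 1: before inclusion; period 2: waiting for results; period 3: during the 12 months following the results". Period 3 has a length; period 1 does not.
- **Table 1.** The objective is worded as "in the first year after the reporting of GS analyses compared to the period before the inclusion", again with no baseline length.
- **Data Analyses, Impact Studies.** "Frequencies of follow-up changes between the period prior to inclusion and the period following the results will be calculated", with 95% confidence intervals, separately in previously explored and never-explored patients.
- **Secondary Outcomes.** The criterion is change in the number and type of medical, medico-social, rehabilitative and psychological care, and the wording attributes that change to the trio results.

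**The concern.** A before-after comparison of how much care patients use, and of what kinds, needs windows of equal length or an adjustment for unequal ones. The objective meets this condition. The methods text, read literally, does not, because its period 1 depends on when each patient first saw a geneticist.

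The two populations would be distorted in opposite directions. Never-explored patients are at a first genetics consultation, and Inclusion places enrolment during a genetics consultation or after a period of reflection, so their period 1 is close to zero. For previously explored patients, period 1 is the whole earlier search, which may exceed a year. Care that had not changed could look like a rise in one half of the cohort and a fall in the other. Ethics and Dissemination expects the impact studies to help support a decision on first-line genome sequencing, so such artefacts could be read as effects of the test.

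**Working it through.** The article gives no sample size, power or effect size for this analysis, so there is no planned figure to reproduce. The check has two parts.

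**1. The definitions side by side**

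| Place | Before window | After window |
|---|---|---|
| Introduction (objective) | 12 months before inclusion | 12 months after results |
| Methods, Impact Studies | period 1: first genetics consultation to inclusion | period 3 |
| Figure 1 caption | before inclusion, no length | 12 months after results |
| Table 1 | before inclusion, no length | first year after results |
| Data Analyses, Impact Studies | before inclusion, no length | after results |

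Only the first two rows fix the baseline, and they disagree. Nothing in the methods or analysis sections restores the one-year window or standardises for time.

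**2. What the methods version does when nothing changes**

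Inputs: period 3 is 12 months (Figure 1 caption). The baseline length L (months) and the care rate r (contacts a year) are not in the article. They are assumed, and shown over a range.

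Expected counts are r in period 3 and r × L/12 in period 1, so the expected ratio is 12/L whatever r is.

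Taking independent Poisson counts, the difference between periods follows a Skellam distribution, which gives the chance that a patient shows an apparent increase or decrease:

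| L (months) | Ratio 12/L | Increase / decrease, r = 1 | Increase / decrease, r = 4 |
|---|---|---|---|
| 1 | 12 | 0.60 / 0.03 | 0.95 / 0.01 |
| 3 | 4 | 0.55 / 0.09 | 0.88 / 0.05 |
| 12 | 1 | 0.35 / 0.35 | 0.43 / 0.43 |
| 24 | 0.5 | 0.18 / 0.61 | 0.09 / 0.85 |
| 36 | 0.33 | 0.09 / 0.78 | 0.01 / 0.97 |

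The type of care is affected as well. For a type used once a year on average, the chance that it is absent in period 1 and present in period 3 is (1 − e^−1) × e^(−L/12):

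- L = 1: 0.632 × 0.920 = 0.58
- L = 12: 0.632 × 0.368 = 0.23
- L = 36: 0.632 × 0.050 = 0.03

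Rates alone do not rescue a near-zero baseline. At L = 1 and r = 4 the expected baseline count is 4 × 1/12 = 0.33, so e^−0.33 = 0.72 of patients would have a baseline rate of zero. A 12-month look-back gives a ratio of 1 and equal chances of increase and decrease.

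**The case against.** The best defence is that the one-year window was intended throughout. The consultation-to-inclusion wording sits in the sentence on the odyssey-cost study, which the analysis section restricts to previously explored patients. The Figure 1 caption defines period 1 only as the time before inclusion, and the objective is the one place that gives this study a baseline length. Period 1 could then be a shorthand label. This is a fair account of likely intent, but it does not remove the conflict: the follow-up study is tied to period 1 in the paragraph that has just described period 1 differently.

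The second defence is that the planned frequencies may be proportions of patients with a change, and that standardisation may be set out in a document not shown. That limits what can be said about size. It does not make window length harmless, since the chance of any apparent change, or of a new type of care, also depends on it.

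A reader might go further in three ways that the documents do not support:

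- **A definite spurious fall in previously explored patients, such as 50% at 2 years or 67% at 3.** These figures need assumed baseline lengths and raw counts. Fuller capture by diary after inclusion could push the other way, and its size is unknown.
- **Period 3 against period 2 as a like-for-like comparison.** Both use a diary and phone contact, but microarray and Fragile-X results reach families as soon as available, and study work-up also falls in period 2.
- **A formal contrast of change between trio-positive and trio-negative patients as a requirement.** Sub-analyses by trio result are already planned. The contrast is optional in a descriptive secondary analysis, and trio-negative patients also receive a result and a dedicated visit.

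**Conclusion.** The concern holds as a contradiction in the current text about the baseline of the before-after study. The methods version would make the number and type of care depend partly on window length, with an expected ratio of 12/L if the care rate is constant and counts are not standardised. The direction follows from the definitions: upward where the baseline is shorter than 12 months, downward where it is longer. The size in this cohort cannot be stated, because the article gives neither the length of period 1 nor care rates. The near-zero baseline in never-explored patients is inferred from inclusion at a first genetics consultation.

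This should be fixed. The analysis is secondary and descriptive. A reader might infer that the main diagnostic-yield result is in doubt; it is not, because the McNemar comparison does not use these periods.

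**What to change.** In both Impact Studies sections (methods and data analyses), define the baseline for the follow-up study as the 12 months before inclusion in both populations, as the objective already says. Align Table 1 and the Figure 1 caption. Keep the first-consultation-to-inclusion span for the odyssey-cost analysis only, under a different label. Use rates per unit of time where a patient's observed time in either window is incomplete.

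The cost is mainly wording. The look-back does need dated pre-inclusion care. The Inclusion section describes history and previous examinations collected at that visit, but does not say that rehabilitation or medico-social care in the previous year is dated. Baseline care is therefore collected retrospectively, whereas after the results "A new diary will be given to the family for the subsequent 12 months". State this difference in capture as a limitation, and do not attribute changes to the results on the before-after comparison alone.
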